#### Analysis of the secondary outcomes

The analysis of the secondary objectives will also be carried out by intention to treat. Qualitative secondary outcomes such as the mortality at day 90 will be described in each group by the event proportion and compared using the *χ*^2^ test or the exact test of Fisher. Quantitative secondary outcomes such the VFD at day 60 will be described in each group by the mean and the standard deviation or the quartiles, and the minimum and maximum values according to the shape of the distribution. They will be compared between the two groups using the *t* test of Student or the test of Mann and Whitney.

All the analyses will be carried out using the SAS software, version 9.4 (Copyright (c) 2002–2003 by SAS Institute Inc., Cary, NC, USA). The comparisons will be considered statistically significant for a bilateral *p*-value < 0.5.

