#### Secondary outcomes

Ninety-day all-cause mortality.VFD at day 60 after inclusion.Time from inclusion to successful extubation.Successful extubation will be defined as extubation without reintubation or death within 48 h in intubated patients and as weaning of invasive mechanical ventilation for at least 48 h in tracheotomized patients.Length of hospital stay from inclusion.Value of respiratory parameters (PaO_2_/FiO_2_ ratio, pH, PaCO_2_, PEEP, VT, total PEEP, plateau pressure, driving pressure, respiratory rate, MP) assessed daily from inclusion to weaning of deep sedation or 14 days after inclusion whichever comes first.Total PEEP and plateau pressure will be measured at the end of 3-s end-expiratory and end-inspiratory pauses, respectively. Driving pressure will be defined as the difference between plateau pressure and total PEEP. MP will be computed as previously described [14], and partitioned into 3 components:
$$ VT-\mathrm{related}\ \mathrm{MP}=0.0098\times RR\times {VT}^2\times \frac{1}{2}{El}_{rs} $$
$$ \mathrm{PEEP}-\mathrm{related}\ \mathrm{MP}=0.0098\  RR\times VT\times {\mathrm{PEEP}}_{\mathrm{tot}} $$
$$ \mathrm{Resistive}\ \mathrm{MP}=0.0098\times {RR}^2\times {VT}^2\times \frac{\left(1+I:E\right)}{60\times I:E}{R}_{\mathrm{aw}} $$

with RR = respiratory rate, *El*_*rs*_ = elastance of the respiratory system = driving pressure/VT, *I:E* = inspiratory-to-expiratory ratio, *R*_aw_ = airway resistance = (peak airway pressure − plateau pressure)/inspiratory flow.

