### Sample size {14}

The sample size was computed through data simulations based on the following hypotheses:
Ninety-day mortality 45% in the control group, and 40% in the intervention group (i.e., relative reduction 11%)Mean ± standard deviation (*SD*) VFD at day 60 28 ± 16.5 in the control group and 34.5 ± 13 in the intervention group

The expected mortality in patients with COVID-19 and moderate to severe ARDS is between 34 and 50% [1]. The mean and *SD* of VFD at day 60 in the control group was taken from the subgroup of patients with PaO_2_/FiO_2_ < 150 mmHg included in the control group of the prospective randomized Xtravent-study comparing ultra-protective ventilation with extracorporeal CO_2_ removal versus conventional protective ventilation [7]. To be conservative, we have chosen to take an expected difference between the two groups of the present study corresponding to 50% of the difference observed in the Xtravent-study between the control and the intervention groups.

For each scenario corresponding to a given sample size, 1000 datasets were simulated. For each simulation, the score was computed for each patient and compared between the two groups using the test of Mann and Whitney. The power was computed as the proportion of tests with a bilateral *p*-value < 0.05.

The results of the simulations allowed us to determine that the inclusion of 100 patients per group will achieve a power greater than 80% to conclude a significant difference between the groups.

The simulations were implemented by two biostatisticians with the SAS software, version 9.4 (Copyright (c) 2002–2003 by SAS Institute Inc., Cary, NC, USA) and the R software, version 3.6.1 (R Core Team (2012)). The results were similar.

To account for premature exits from the study (withdrawal of informed consent for example), we have planned to add 10% more patients (10 supplementary patients in each group for a total of 220 patients).

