## Statistical methods

### Statistical methods for primary and secondary outcomes {20a}

#### Descriptive analysis

Patients’ characteristics will be described and compared between the two groups to verify the allocation efficacy. Quantitative characteristics will be described using the following statistics: number of missing data, mean, standard deviation, quartiles, and minimum and maximum values. Qualitative characteristics will be described using the following statistics: number of missing data and absolute and relative frequency in each category. Quantitative characteristics will be compared between the two groups using the *t* test of Student or the test of Mann and Whitney. Qualitative characteristics will be compared using the *χ*^2^ test or the exact test of Fisher.

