### Methods for additional analyses (e.g., subgroup analyses) {20b}

Exploratory analysis regarding the primary outcome will be performed by comparing both arms of the study in the following subgroups of patients: age greater or lower than its median value, SAPS2 greater or lower than its median value, SOFA score at randomization greater or lower than its median value, renal SOFA at randomization < 2 and ≥ 2, bicarbonates at randomization < 22 and ≥ 22 mmol L^−1^, driving pressure at randomization greater or lower than its median value, plateau pressure at randomization greater or lower than its median value, compliance of the respiratory system at randomization greater or lower than its median value, mechanical power at randomization greater or lower than its median value, PaO_2_ at randomization ≤ 100 mmHg and > 100 mmHg, and pH at randomization greater or lower than its median value.

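### The daily respiratory outcomes are compared without adjusting for each patient's recorded value at randomisation: a valid test, but one that gives up precision

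*Protocol article*

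**What the plan says.** Secondary outcome 5 is a set of ten respiratory parameters: gas exchange (PaO2/FiO2, PaCO2, pH), ventilator settings (VT, respiratory rate, PEEP) and mechanics (total PEEP, plateau and driving pressure, mechanical power). Their schedule reads "assessed daily from inclusion to weaning of deep sedation or 14 days after inclusion whichever comes first". Objectives {7} states as an aim to test whether ULTV affects them.

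Analysis of the secondary outcomes treats quantitative secondary outcomes as one class, with VFD as its example: "They will be compared between the two groups using the *t* test of Student or the test of Mann and Whitney". The article contains no ANCOVA, mixed model or other baseline-adjusted analysis.

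Baseline values exist. The subgroup section {20b} lists "driving pressure at randomization greater or lower than its median value, plateau pressure at randomization greater or lower than its median value". It splits patients in the same way on mechanical power and on pH, and all these splits are for subgroups of the primary outcome. PaO2/FiO2 is also needed for eligibility. Under Descriptive analysis, "Patients’ characteristics will be described and compared between the two groups to verify the allocation efficacy", but no adjustment follows from that comparison.

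**The concern.** These outcomes carry the trial's mechanistic and physiological-safety answer: whether ULTV lowers driving pressure and mechanical power, and what happens to pH, PaCO2 and oxygenation. A patient's lung mechanics and gas exchange after randomisation may well be related to the values just before it. A raw two-group comparison leaves that between-patient variation in the error term, so its intervals are wider than the collected data allow. In the one randomisation that is actually drawn, it also carries a share of any chance baseline difference into the estimate. Because the series starts at inclusion, a value taken before the settings change could also be counted as an outcome.

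**Working it through.** **The plan's own figure.** The article states no power or target difference for the respiratory outcomes. Its only power figure, above 80% with 100 per group, belongs to the primary composite score. Simulating the procedure as described under Sample size {14} gave 81% to 82%. That figure concerns another endpoint and another test. It says nothing about the respiratory outcomes, and whether the score test holds its level is a separate matter.

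**Inputs.**
- n = 100 per arm, 1:1 (Sample size {14}, Trial design {8}).
- Two-sided alpha 0.05, from Sample size {14}: "The power was computed as the proportion of tests with a bilateral *p*-value < 0.05". The analysis section prints 0.5 instead; 0.05 is used here.
- rho: not in the article. Assumed at 0.3, 0.5 and 0.7, with 0 as the floor.
- Model: one follow-up value per patient, linear in baseline with a common slope, and the same SD at both times.

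**Step 1: reference difference.** The difference that the raw t test detects with 80% power is (1.960 + 0.8416) × √(2/100) = 2.8016 × 0.1414 = 0.396 SD. This is a convenient reference, not a target of the trial.

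**Step 2: gain from adjustment.** ANCOVA multiplies the residual variance by 1 − rho². Power = Φ(2.8016/√(1 − rho²) − 1.960).

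| rho | Variance ratio | ANCOVA power (formula) | Simulated: raw test | Simulated: ANCOVA | n per arm for 80% power |
|---|---|---|---|---|---|
| 0 | 1.00 | 80.0% | – | – | about 100 |
| 0.3 | 0.91 | 83.6% | 79.7% | 83.0% | 91 |
| 0.5 | 0.75 | 89.9% | 79.5% | 89.4% | 75 |
| 0.7 | 0.51 | 97.5% | 79.3% | 97.3% | 51 |

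Each simulated figure rests on 20,000 datasets. With no true difference, both tests rejected in about 5% of datasets (4.9% to 5.2%).

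**Step 3: effect of a chance imbalance.** The standard error of the baseline difference is √(2/100) = 0.141 SD. If the arms differ at baseline by q standard errors, the raw estimate shifts by rho × q × 0.141 SD. The conditional type I error is 1 − Φ((1.96 − rho·q)/√(1 − rho²)) + Φ((−1.96 − rho·q)/√(1 − rho²)).

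| Imbalance | Quantity | rho 0.3 | rho 0.5 | rho 0.7 |
|---|---|---|---|---|
| 1 SE (0.141 SD) | Shift, SD | 0.042 | 0.071 | 0.099 |
| 1 SE | Conditional type I error | 5.0% | 4.8% | 3.9% |
| 1.96 SE (0.277 SD) | Shift, SD | 0.083 | 0.139 | 0.194 |
| 1.96 SE | Conditional type I error | 7.9% | 12.9% | 20.5% |

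An imbalance of 0.2 SD is 0.2/0.141 = 1.41 SE. It is reached or exceeded in either direction with a chance of about 16% for any one parameter, and shifts the raw estimate by 0.5 × 0.2 = 0.10 SD at rho 0.5.

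**Step 4: where the gain is likely small.** VT, PEEP and respiratory rate are set or steered by the ventilation procedure (Table 1). The entry criteria narrow the baseline range of VT (at most 6 mL/kg), PaO2/FiO2 (at most 150 mmHg) and pH (patients below 7.21 at a rate of 35/min are excluded).

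**The case against.** The sentence on secondary outcomes is generic. Its example, VFD, has one value per patient. It never mentions the daily series, the day to be compared or how up to 14 days of values are handled, and the full protocol, in an additional file, is not shown. So it would be too strong to say that the article permits nothing but a raw test. What stands is that the sentence names a test for the whole class, that the respiratory parameters are in the class, and that the article offers no alternative. An adjusted analysis would depart from the stated test rather than fill a gap.

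A reader might infer that the raw comparison is biased, or that baseline imbalance would be mistaken for a ULTV effect. The article does not support that. Allocation is randomised, the raw test is unbiased over randomisations, and its error rate is about 5%. At an imbalance of one standard error the conditional error rate does not exceed 5%. Only a large imbalance combined with a sizeable rho raises it.

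The size is not anchored in this trial: rho and the 0.396 SD reference are both assumed, and the figures are for a single time point with all 100 patients per arm contributing. That objection stands in full.

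Baseline adjustment also does not solve the harder problem in this outcome. Series end at weaning of deep sedation or at death, and both are related to outcome. A mixed model over all days to day 14 would rest on a missing-at-random assumption that is hard to interpret after death. This stands too, and it shapes the fix.

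**Conclusion.** The point holds as a question of efficiency. The article names an unadjusted test for a class that includes the respiratory outcomes, although baseline values are already recorded for at least four of them. The cost is lost precision, plus a shift of rho times whatever imbalance is drawn.

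If rho lies between 0.3 and 0.7, adjustment raises power from 80% to between 84% and 98% for a difference of 0.396 SD at 100 per arm. At rho 0 the gain is nil, and for the steered and range-restricted parameters it is probably small. These figures assume a linear relation with baseline, a common slope and complete data at one time point.

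This is a minor improvement to secondary outcomes. It corrects no invalid test and leaves the primary conclusion unaffected.

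**What to change.** For the respiratory outcomes, replace the raw test with an ANCOVA that has the patient's own value at randomisation as covariate, on the log scale where the parameter is skewed. Report the adjusted between-arm difference with its 95% confidence interval. Do not count the value at randomisation as a post-treatment observation.

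Make the main comparison on early post-randomisation days, before the daily deep-sedation weaning trials start on day 3 (Intervention description {11a}), when few series should have ended. Treat any repeated-measures model to day 14 as supportive, and describe it as conditional on being alive and still under deep sedation.

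The cost is a few sentences in the analysis section. Before making the change, confirm that the value at randomisation is held for every parameter, since the subgroup list does not name all ten. No extra patients, visits or measurements are needed for those already recorded.

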### Objectives {7}

The main objective is to assess the benefit of ULTV in comparison with protective ventilation on a composite primary endpoint that will include the all-cause mortality at day 90 as the prioritized criterion and the number of days free from invasive mechanical ventilation (VFD) at day 60 as the second criterion.

The following are the secondary objectives:
To test whether ULTV is associated with a decrease in ARDS all-cause mortality at day 90 after inclusionTo test whether ULTV is associated with higher VFD at day 60 after inclusionTo test whether ULTV is associated with a decrease in time to successful extubationTo test whether ULTV is associated with a shorter hospital stayTo test whether ULTV impacts the following respiratory parameters assessed daily from inclusion to weaning of deep sedation or 14 days after inclusion whichever comes first (PaO_2_/FiO_2_ ratio, pH, PaCO_2_, positive end-expiratory pressure (PEEP), VT, total PEEP, plateau pressure, driving pressure, respiratory rate, mechanical power (MP))To test whether ULTV is associated with an increase in sedation dose during the first 14 days after inclusionTo test whether ULTV is associated with an increase in rescue therapy during the first 14 days after inclusionTo test whether ULTV is associated with a decrease in the incidence density rate of adverse events during the first 28 days after inclusion (severe mixed acidosis, ventilator-associated pneumonia, acute cor pulmonale, barotrauma, any serious adverse events)To test whether ULTV is associated with cognitive impairment at day 365 after inclusionTo test whether ULTV is associated with quality-of-life impairment at day 365 after inclusionTo test whether ULTV is associated with post-traumatic stress disorder at day 365 after inclusionTo evaluate the efficiency of the innovative strategy performing a cost-effectiveness analysis at day 90 after inclusion

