### Adverse event reporting and harms {22}

Based on the pilot trial on 34 patients [8], the following adverse events are suspected to increase or decrease in association with the intervention: severe mixed acidosis, ventilator-associated pneumonia, acute cor pulmonale, and barotrauma. These expected adverse events will be collected systematically and daily in the eCRF from day 1 to day 28 of the study as long as the participants remain mechanically ventilated. Given their high frequency in relation with the severity of the underlying disease, the following non-serious adverse events will not be reported: acute kidney injury with KDIGO grade < 3, metabolic disorders, non-fatal nosocomial infections (with the exception of bacteremia and ventilator-associated pneumonia), shock (with the exception of those related to acute cor pulmonale), non-fatal worsening of respiratory condition, and ICU-acquired weakness. All other adverse events occurring from inclusion to hospital discharge will be reported through a spontaneous report.

Serious adverse event (SAE) information will be collected for the duration of the participant’s involvement in the trial. SAEs will be managed according to the best current standard of care and reported to the sponsor according to good clinical practices. All SAEs will be reported to the sponsor within one business day, in a structured narrative explaining the events that occurred. An internal safety monitor will adjudicate all SAEs for report completeness, seriousness of event, and relationship to study interventions. After receiving an unexpected SAE report, the sponsor will notify to the French regulatory agencies and the research ethics committee (CPP Ile de France 7).

Expected adverse events, SAEs, and non-serious adverse events will be reported in trial publication.

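### Hospital stay, time to extubation and adverse-event rates fall, by class, under tests that make no allowance for death or time at risk

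*Protocol article*

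**What the plan says.** All references are to the protocol article.

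- **Tests.** Analysis of the secondary outcomes divides these outcomes into two classes. Qualitative outcomes, with day-90 mortality as the example, are described by the event proportion and compared by χ² or Fisher. For quantitative outcomes, with VFD as the example: "They will be compared between the two groups using the *t* test of Student or the test of Mann and Whitney". There is no third class.
- **Outcomes.** The Secondary outcomes section lists "Time from inclusion to successful extubation" and length of hospital stay from inclusion. Death enters the extubation definition only through the 48-hour window after extubation. No value or rule is given for a patient who dies intubated or dies in hospital. Section {20c} rules out imputation of missing data.
- **Adverse events.** Objectives {7} asks whether ULTV is associated with a "decrease in the incidence density rate of adverse events during the first 28 days after inclusion". Adverse event reporting and harms {22} collects the four expected events (severe mixed acidosis, ventilator-associated pneumonia, acute cor pulmonale, barotrauma) "from day 1 to day 28 of the study as long as the participants remain mechanically ventilated". The same section collects serious adverse events throughout participation.
- **Planned mortality.** Sample size {14} assumes "Ninety-day mortality 45% in the control group, and 40% in the intervention group".

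**The concern.** Death is frequent here, and it ends both hospital stay and the chance of extubation. If it is ignored, three things follow.

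- **Hospital stay.** A patient who dies early contributes a short stay, and the objective treats a shorter stay as the good result.
- **Time to extubation.** A t or Mann-Whitney test needs a number for each patient. Those who die intubated have none, so the comparison rests on patients who reached extubation. That group is formed after randomisation, and treatment can affect who is in it. This sits poorly with the intention-to-treat statement in the same section.
- **Adverse events.** The objective is a rate, but the only event method stated has no time in the denominator. For the four expected events the observation window closes when ventilation ends, and ventilation time is something the trial hopes to change.

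At stake is the reading of three secondary objectives. The article already solved the problem for VFD, which is set to 0 for death by day 60, but not for these outcomes.

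**Working it through.** **The plan's own figure.** The article gives no figure for these secondary outcomes. Its one computed figure is for the primary outcome: "the inclusion of 100 patients per group will achieve a power greater than 80"%, from VFD of "28 ± 16.5 in the control group and 34.5 ± 13 in the intervention group", where "The power was computed as the proportion of tests with a bilateral *p*-value < 0.05". Simulation following that description gave 81%, 82%, 82% and 92% for four assumed shapes of the VFD distribution, so the figure reproduces by the stated procedure. The present point does not depend on it. Rejection percentages below use two-sided 0.05 and 100 patients per arm.

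**1. Hospital stay.** From the plan: mortality 45% and 40%. Assumed: deaths at day 15, survivors discharged at day 40, the same in both arms.

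Mean stay = (proportion dying × day of death) + (proportion surviving × day of discharge)

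- Control: 0.45 × 15 + 0.55 × 40 = 6.75 + 22.00 = 28.75 days
- ULTV: 0.40 × 15 + 0.60 × 40 = 6.00 + 24.00 = 30.00 days
- Difference: +1.25 days

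The difference equals 0.05 × (discharge day − death day). It is 0.05 × 30 = 1.5 with deaths at day 10 and 0.05 × 20 = 1.0 with deaths at day 20.

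The result depends on survivors' stay not changing. If that stay also fell by the planned VFD difference (34.5 − 28 = 6.5 days), the ULTV mean would be 0.40 × 15 + 0.60 × 33.5 = 26.1 days, which is 2.65 days shorter than control. The two effects cancel when survivors' stay falls by 1.25 / 0.60 ≈ 2.1 days.

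**2. Time to extubation.** The article does not fix how many patients would have no extubation time. Assumed: constant competing hazards, total 1/32 per day in control, split 55% extubation and 45% death (3,000 simulated trials per scenario).

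- *Deaths before extubation cut to 40%, same total hazard.* The proportion extubated rises from 55% to 60%. The median time among the extubated is 22.4 days in control and 22.5 under ULTV, and Mann-Whitney on the extubated rejects in 4.9%. The comparison does not register the benefit.
- *Stress case: same extubation hazard, death hazard doubled under ULTV.* The proportion extubated falls from 55% to 38% (0.55 / 1.45). The median among the extubated falls from 22.4 to 15.5 days, an apparent improvement, and Mann-Whitney rejects in 33%. This shows what can happen; it is far from the planned effect.

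**3. Adverse events.** Assumed: the same daily rate r in both arms (rate ratio 1), different ventilated days d within the 28-day window. Proportion with an event = 1 − exp(−r × d). Rejection is from the usual power formula for two proportions.

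| r per day | 20 vs 28 days: proportions | rejects | 22 vs 26 days: proportions | rejects |
|---|---|---|---|---|
| 0.01 | 18% vs 24% | 19% | 20% vs 23% | 8% |
| 0.02 | 33% vs 43% | 30% | 36% vs 41% | 11% |
| 0.03 | 45% vs 57% | 38% | 48% vs 54% | 13% |

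With equal days at risk, rejection is 5%. With unequal days the proportions differ although the rate named in the objective does not.

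**The case against.** The strongest reply is that the article assigns tests by class, with examples, and names none of these three outcomes. A time to event or an incidence density is not obviously qualitative or quantitative, so the text could be read as silent, and silence on such methods is normal when the analysis plan and full protocol are not shown. It is right that the coverage is by class and not by name. But the section does not defer: it offers two classes for the secondary outcomes and no other. Hospital stay is plainly quantitative, time to extubation is a number of days, and the only event method is a comparison of proportions.

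Four stronger readings are tempting, and the documents do not support them.

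- *The extubation test would use at most 55 to 60 of 100 patients per arm.* Those are planned 90-day survivors. A patient who is extubated successfully and dies later still has an extubation time, so this is not an upper limit.
- *All adverse events are recorded only while ventilated.* That holds for the four expected events. Serious adverse events are collected throughout participation, and other reportable events until hospital discharge.
- *A mortality benefit must lengthen mean stay.* It does so only if survivors' stay is not shortened enough to offset it.
- *The article says that patients who die intubated are dropped.* It does not say so. This follows from applying the stated tests without imputation or a rule for death.

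It is also fair that mortality and VFD are reported beside these outcomes, which limits the risk of misreading, and that the choice among competing-risk measures is partly preference.

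**Conclusion.** The point holds as a recommended change to secondary analyses. The primary outcome ranks death first and is not affected.

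Followed as written, the scheme lets in-hospital death count as a shorter stay, confines the extubation comparison to a subset formed after randomisation, and tests proportions where the objective is a rate.

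The sizes are illustrations. Mean stay is 1.25 days longer from the planned mortality reduction alone (1.0 to 1.5 over deaths at days 20 to 10), if survivors' stay is unchanged; the sign can reverse if it is not. For expected adverse events with equal rates, false rejection is 8% to 13% at 22 versus 26 ventilated days and 19% to 38% at 20 versus 28. The days, hazards and event rates are assumptions; only the mortality and VFD figures come from the article.

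**What to change.** Replace the two-class rule for these outcomes in the analysis text:

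- **Time to successful extubation and time to discharge alive:** treat death as a competing event. Show cumulative incidence by arm, with cause-specific and/or subdistribution hazard ratios and 95% confidence intervals. State in advance which measure is the main one.
- **The four expected adverse events:** rates per ventilated patient-day up to day 28, compared by Poisson or negative binomial regression with log ventilated days as offset.
- **Serious adverse events:** rates per day of follow-up up to day 28, with log follow-up time as offset, because they are not restricted to ventilated time.
- **Alongside the rates:** the 28-day proportions by arm, because ventilated time may itself be affected by treatment.

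The cost is a change of analysis wording and standard software. The outcomes already require dates of extubation, discharge and death. The case report form is not shown, so check that it gives ventilated days and follow-up days to day 28 for each patient.

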#### Analysis of the primary outcome

The main analysis will be carried out by intention to treat, i.e., all the patients included in the study will be analyzed in their initial randomization group regardless of whether the allocated ventilation strategy was effectively applied or not.

The distribution of the composite score will be described in each group using the following statistics: mean, standard deviation, quartiles, and minimum and maximum values. It will be compared between the two groups using the test of Mann and Whitney.

The ULTV effect size will be quantified by the probability of a favorable result for a patient belonging to the ULTV arm in comparison with a patient belonging to the protective ventilation arm. This probability will be estimated by the proportion of pairs for which the patient of the ULTV arm will have a favorable result [20]. This estimate will be given with a 95% confidence interval.

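### The statistical methods print a two-sided significance threshold of 0.5, which contradicts the 0.05 used for the power and the 95% confidence interval for the primary effect

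*Protocol article*

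**What the plan says.** The significance rule is the last sentence of the protocol article's section Analysis of the secondary outcomes: "The comparisons will be considered statistically significant for a bilateral *p*-value < 0.5". The sentence before it names the software and has a general scope: "All the analyses will be carried out using the SAS software, version 9.4".

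Two other places fix a level:

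- Sample size {14}, on the simulations: "The power was computed as the proportion of tests with a bilateral *p*-value < 0.05". The test simulated is the one planned for the primary outcome: "the score was computed for each patient and compared between the two groups using the test of Mann and Whitney". The sample size rests on that level: "the inclusion of 100 patients per group will achieve a power greater than 80" per cent.
- Analysis of the primary outcome, on the effect size: "This estimate will be given with a 95% confidence interval". That section names the Mann-Whitney test but gives no threshold of its own.

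Interim analyses {21b} says that none is planned. The article describes no division of alpha and no looser level for exploratory comparisons.

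**The concern.** The printed rule is the only significance criterion in the statistical methods part of the article, and it is ten times the level behind the sample size. The article says that it was published to guard against selective reporting and data-driven analysis. A reader who later checks the reported conclusions against the published plan would find a rule under which almost any difference of modest size counts as significant. The rule also clashes with the planned interval: a result could be significant as printed while its 95% confidence interval includes no effect. Because the rule follows a sentence about all the analyses and the primary section has no threshold, the natural reading extends it to the primary outcome, although the text does not say so.

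**Working it through.** **Inputs.** Printed threshold 0.5 (Analysis of the secondary outcomes). Threshold behind the power 0.05, 100 patients per group, power above 80% (Sample size {14}). Mortality: "Ninety-day mortality 45% in the control group, and 40% in the intervention group". Ventilator-free days (VFD) 28 with SD 16.5 in the control group and 34.5 with SD 13 in the intervention group (same section). Confidence level 95% (Analysis of the primary outcome).

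**Step 1: the plan's own figure.** The simulation used 4,000 datasets per scenario. Death was Bernoulli, and survivors' VFD were normal, run both unrounded and rounded and clipped to 0–60. The VFD mean and SD were taken to describe survivors. This is an assumption: with 45% zeros and an overall mean of 28, the overall SD could not be below 28 × √(0.45/0.55) = 25.3, yet 16.5 is stated. Scoring each patient against the other group only, as the article defines the score, and then applying Mann-Whitney gave:

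| Patients per group | Share with p < 0.05 | Share with p < 0.5 |
|---|---|---|
| 60 | 75.0% | 92.0% |
| 80 | 77.9% | 92.7% |
| 100 | 80–82% | 94% |

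The stated power is reproduced at 0.05 with 100 per group. At 0.5, 60 per group would already have exceeded 80% by a wide margin. The sample size was therefore set at 0.05, as its section says.

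**Step 2: the statements side by side.**

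| Place | Two-sided level | Critical value of z |
|---|---|---|
| Sample size {14} | 0.05 | 1.960 |
| Analysis of the primary outcome (95% interval) | 1 − 0.95 = 0.05 | 1.960 |
| Analysis of the secondary outcomes | 0.5 | 0.674 |

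The ratio is 0.5 / 0.05 = 10. An interval matching 0.5 would be a 50% interval. For a statistic that is approximately normal, any |z| between 0.674 and 1.960 is significant under the printed rule while the 95% interval covers no effect.

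**Step 3: what the printed rule would do to a valid test.** For a continuous test statistic, the p-value under the null is uniform, so P(p < 0.5) = 50% and P(p < 0.05) = 5%. The difference is 50 − 5 = 45 of every 100 true-null comparisons. As a check, all patients were ranked jointly (death worst, then VFD) under no effect, with 100 per group. Mann-Whitney rejected 49.7% and 51.9% in two runs at 0.5, and 5.5% and 5.8% at 0.05. A separate repeat gave 51% and 4.7%. Discrete tests such as Fisher's exact test reject somewhat fewer.

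**Step 4: why these rates do not carry over to the primary test.** The score compares each patient only with the other group, so the two groups' scores are built from each other and are not independent. Under no effect, Mann-Whitney on those scores rejected about 88% at 0.05 and 96% at 0.5 (89% and 97% in a repeat). For the primary test as written, 0.5 does not give 50% and 0.05 does not give 5%.

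**The case against.** The strongest reply is that this is a misprint and not a decision. The article shows the intended level twice, once for the very test used on the primary outcome, and a trial statistician is very unlikely to apply 0.5. The 50% rate is therefore what a literal reading implies and not an expected property of the trial. That stands. It bears on how likely harm is, not on whether the published rule is right: the article states the rule, states it wrongly and nowhere corrects it.

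It can also be said that the sentence sits under the secondary outcomes and that the all-analyses sentence before it concerns software. That stands in part: extension to the primary outcome is the natural reading but not an explicit one, so the correction should state the scope.

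Three stronger readings are tempting, and the documents do not support them.

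- A reader might infer that the printed 0.5 overrides the other two places and governs the conclusions. No text gives it precedence. The article simply contradicts itself.
- A reader might infer that the primary test would run at a type I error of 50% instead of 5%. The dependence between the groups' scores rules out both figures.
- A reader might treat the 12 secondary objectives as 12 independent tests and compute 1 − 0.5^12 = 99.98% for at least one false positive, against 1 − 0.95^12 = 46.0%. The list does not fit that model. One item is a cost-effectiveness ratio, which is not obviously a between-group test, one holds ten respiratory parameters, one holds several adverse events, and mortality, VFD, time to extubation and length of stay can be expected to be correlated. Multiplicity is in any case a different question from this misprint.

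**Conclusion.** Wrong as written. The printed threshold of 0.5 contradicts the 0.05 behind the sample size and the 95% interval for the primary effect, and nothing in the article accounts for it. It is probably a slip for 0.05. The contradiction itself rests on no assumption. Its size, about 50% instead of 5% per true-null comparison, assumes a literal reading and a valid test with a near-continuous p-value, and is somewhat smaller for discrete tests. It describes valid tests of secondary outcomes and makes no claim about the primary test. Restoring 0.05 removes the contradiction. It does not by itself secure the type I error of the primary comparison, which has to be settled as a separate point.

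**What to change.** In Analysis of the secondary outcomes, replace 0.5 with 0.05 and state the scope, for example: comparisons for the primary and the secondary outcomes are declared significant when the two-sided p-value is below 0.05. This agrees with the sample size section and with the 95% interval. Check the full protocol (Additional file 2) and any statistical analysis plan for the same slip.

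The cost is one digit and a clause, by erratum or a line in the analysis plan. Recruitment, data collection, the sample size of 220 and the choice of tests are unaffected.
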